### Economic analysis

An economic analysis will be carried out from a societal perspective with costs classified as either payer (costs born by the province) or non-payer (costs born by individuals or the families of children with croup). The analysis will include all health care costs, costs borne by the family, and costs stemming from the strategies for implementing guidelines.

#### Potential benefits

Potential benefits will be considered to be the duration of croup symptoms and the absence of any severe adverse outcomes among children.

#### Overview of costing methods

Costing information will be gathered in sufficient detail to allow a comparison of costs and benefits. The form that the analysis will take will depend on the relative ratios of cost versus benefit. For example, if either of the two experimental strategies (non-standard) achieve similar or better clinical outcomes at decreased or equal costs as the standard dissemination strategy, the experimental interventions will be judged as cost-effective. Alternatively, if the experimental interventions yield increased benefits at increased costs, a ratio of the incremental cost per outcome gained will be calculated. And last, if the experimental interventions yield decreased benefits but are associated with increased or equal costs, the standard dissemination strategy will be judged to be the most cost-effective. (Please note we have specifically avoided using any reference to either cost-effective analysis or cost-benefit analysis. [5,6])

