#### Economic analysis

To determine which of the three intervention strategies will most effectively reduce total societal costs including all health care costs, costs borne by the family, and costs stemming from the strategies for disseminating guidelines. The null hypothesis is that neither the intermediate nor the high intensity interventions will consume less resources than the low intensity intervention. The alternate hypothesis is that the intermediate intervention will consume fewer resources than either the low intensity intervention or the high intensity intervention.

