#### The three intervention strategies

The intervention strategies to be compared will be a) mailing of printed educational materials (PEMs) (low intensity intervention); b) mailing PEMs plus a combination of interactive educational meetings, educational outreach visits, and reminders (intermediate intensity intervention); and c) mailing PEMs, interactive sessions, outreach visits, reminders plus identification of local opinion leaders (high intensity intervention.

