##### Low intensity intervention

The low intensity intervention is the current strategy utilized by the *Alberta Medical Association Clinical Practice Guidelines Program *for disseminating new guidelines. This intervention arm will serve as a "control". The Croup Guidelines will be mailed to each physician registered with the *Alberta College of Physicians and Surgeons*. The Guidelines will also be available on the *Alberta Medical Association Clinical Practice Guidelines Website*.

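### The only rule linking cost to benefit sets the intensive strategies against standard mailing, so it can pass the high strategy even when the intermediate one dominates it

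*Protocol article*

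**What the plan says.** The protocol's overall aim is to set out the costs and benefits of three strategies. Its economic objective (Aim and objectives, Economic analysis) is to find which of the three most reduces total societal cost. The alternate hypothesis there is that "the intermediate intervention will consume fewer resources than either the low intensity intervention or the high intensity intervention".

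Overview of costing methods then says how cost and benefit will be put together, in three limbs:

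- **Limb 1** opens "For example, if either of the two experimental strategies (non-standard) achieve similar or better clinical outcomes". The full condition and verdict are that if they "achieve similar or better clinical outcomes at decreased or equal costs as the standard dissemination strategy, the experimental interventions will be judged as cost-effective".
- **Limb 2** reads "if the experimental interventions yield increased benefits at increased costs, a ratio of the incremental cost per outcome gained will be calculated".
- **Limb 3** covers less benefit at equal or higher cost, in which case "the standard dissemination strategy will be judged to be the most cost-effective".

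The standard strategy is the mailed guideline: the section Low intensity intervention describes that arm as current practice and as the control. The arms are cumulative. The three intervention strategies section defines high as "mailing PEMs, interactive sessions, outreach visits, reminders plus identification of local opinion leaders", and the section High intensity intervention adds a local consensus process. Calculation of societal costs plans a Laird-Ware model testing whether costs differ between the three groups, with baseline cost as covariate.

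**The concern.** A decision-maker choosing among three mutually exclusive, cumulative strategies needs to know, for high, whether opinion leaders and the consensus process are worth their cost on top of what intermediate already delivers. A comparison of high with mailing credits high with the effect of the components it shares with intermediate. No limb compares high with intermediate. Two faults follow if the rule is applied as written: limb 1 can give both intensive strategies the same favourable verdict with no means of choosing between them, and a limb 2 ratio against mailing can conceal an expensive last step. The recommendation on which strategy to adopt is at stake. The primary outcome, hospital days per 1,000 disease episodes, is not affected.

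**Working it through.** The protocol gives no cost, benefit, ratio or threshold, so there is no stated figure to reproduce. All numbers below are assumptions: cost per episode, and benefit in arbitrary units gained over low. Low is 200 with benefit 0 throughout.

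For high (H) over intermediate (I), the step ratio is (C_H − C_I)/(B_H − B_I). Against low (L), the ratio is (C_H − C_L)/(B_H − B_L).

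**Limb 1, with intermediate at cost 150 and benefit 4, and high at cost 195**

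| Benefit of high | Limb 1 verdict on I and H | High over intermediate |
|---|---|---|
| 4 | both cost-effective | 45 more, no added benefit: dominated |
| 4.5 | both cost-effective | 45/0.5 = 90 per unit |
| 3 | both cost-effective | 45 more and 1 unit worse: dominated |

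Both strategies pass in each row because 150 and 195 are below 200 and both benefits exceed 0. In rows 1 and 3 high should be rejected outright. The pattern is compatible with the plan's own alternate hypothesis, since intermediate is cheaper than both others in all three rows. The wording of limb 1 adds to the problem: its condition is met if either strategy qualifies, while its verdict is given to the experimental interventions together.

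**Limb 2, read with mailing as comparator, with intermediate at cost 210 and benefit 4**

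| High (cost, benefit) | I over L | H over L | H over I |
|---|---|---|---|
| 250, 5 | 10/4 = 2.5 | 50/5 = 10 | 40/1 = 40 |
| 290, 4.5 | 10/4 = 2.5 | 90/4.5 = 20 | 80/0.5 = 160 |
| 220, 8 | 10/4 = 2.5 | 20/8 = 2.5 | 10/4 = 2.5 |

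**General form.** If the intermediate-to-high step carries a share c of high's extra cost over low and a share f of its extra benefit, the step ratio divided by the high-versus-low ratio is c/f. With c = 0.8:

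- f = 0.05: 0.8/0.05 = 16
- f = 0.10: 8
- f = 0.20: 4
- f = 0.50: 0.8/0.50 = 1.6

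When c = f the two ratios agree and nothing is hidden. When c < f the step is cheaper per unit than the average. Intermediate is then extendedly dominated, and high against low is the right comparison. A sequential rule handles all of these cases; a fixed comparison with mailing handles only the last two.

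**Coverage.** Crossing benefit (more, similar, less) with cost (higher, equal, lower) leaves two cells without a limb: similar benefit at higher cost, and less benefit at lower cost.

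**The case against.** Several points on the other side are sound.

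- The limbs are introduced as an example, and the section says the form of the analysis will depend on how costs and benefits turn out. Gaps in a list of examples are weaker evidence than gaps in a closed rule. This stands, but no other rule is given, and two of the three limbs assign verdicts.
- The ratio limb names no comparator. Mailing is an inference from its position between two limbs that do name it, and the sentence does not forbid a ratio against intermediate. It also sets no threshold and gives no verdict. So the label of cost-effective comes from limb 1 alone. The fault in limb 2 is a potentially misleading figure, not a wrong verdict.
- A reader might infer that the whole economic plan compares only with mailing and ignores intermediate versus high. The document does not support that. The alternate hypothesis names that contrast, and the Laird-Ware analysis covers costs in all three arms, so it could show high to be dearer than intermediate. What it cannot show is whether the extra cost buys extra benefit, because it has no benefit term.
- A reader might also infer that the missing cell for less benefit at lower cost collides with the hypothesis that intermediate is cheapest. It does not: that hypothesis predicts lower resource use, not lower benefit, and cheaper with similar or better outcomes falls under limb 1.
- An article may leave the technicalities of dominance and sequential ratios to a fuller economic plan. That excuses missing detail. It does not excuse a stated rule whose named comparator does not fit the three-way question.

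**Conclusion.** The concern holds for the decision rule in Overview of costing methods, not for the economic section as a whole. Applied literally, limb 1 can endorse high when intermediate is cheaper and at least as good, and nothing in the protocol plans a cost per outcome of high over intermediate or a dominance check between them. The size cannot be derived from the document. If the last step carries 80% of high's extra cost and 5% to 50% of its extra benefit, the step ratio is 16 to 1.6 times the ratio against mailing; with proportional growth there is no distortion. The limb 2 part also rests on reading mailing as its comparator. The point matters because the stated overall aim is economic, and it is inexpensive to put right.

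**What to change.** Replace the three limbs in Overview of costing methods with a sequential rule:

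1. Order the three strategies by mean societal cost.
2. Remove any strategy that is dominated (at least as costly and no better than another, and strictly worse on cost or benefit) or extendedly dominated.
3. Report the incremental cost per outcome of each remaining strategy against the next cheaper remaining one.
4. State how results that are cheaper but less effective, and dearer with similar benefit, will be reported, and give the conclusion for each strategy separately.

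The alternate hypothesis needs no change, since it already includes intermediate versus high. The cost is a rewording and one further contrast on data already planned. The downside for the sponsor is that the high strategy may look less favourable than it would against mailing alone.

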#### Health care costs

Payer costs resulting from the provision of health care will be estimated by first determining from the administrative database the total number of physician visits, emergency department visits, days of hospitalization, patient transports, and days in an intensive care unit (Edmonton or Calgary only). Costs per physician visit will be based on the Alberta physician fee schedule. Costs per emergency department visit, and hospital day will be based on published standards for Alberta.[7] Costs for drugs, radiographs, and laboratory tests will be based on provincial standards. For the Edmonton and Calgary hospitals included in the randomised trial and for any intensive care patients, specific hospital case costing is available thereby allowing a unique cost estimate for each patient. Air transport costs will be estimated to be $8 per air mile.

#### Implementation strategy costs

Costs of the three-implementation strategies will be classified as either as payer and non-payer based on whether or not the province assumes responsibility for the cost. They will be estimated from the costs of publication and mailing of questionnaires or learning materials, and the time spent in meetings, organising, travel, and preparing for presentations by the Alberta Medical Association support staff, Regional Quality Assurance staff, "local champions", opinion leaders, and any associates. (The hourly wage will be assumed to be $100 per hour for physician time and to be the mean provincial wage for other health care professionals and administrators.)

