##### Intermediate intensity intervention

The intermediate intensity intervention utilizes techniques that have consistently shown at least a moderate impact on professional behavior. We will work through existing organizational structures in order to more closely simulate how the *Alberta Medical Association Clinical Practice Guidelines Program *might disseminate future guidelines. More specifically, the *Alberta Medical Association Clinical Practice Guidelines program *and the Croup clinical practice guideline committee will work with the Universities of Calgary and Alberta Continuing Education Programs to develop an interactive educational program for physicians, nurses, and respiratory therapists. Utilizing the existing Continuous Quality Improvement Staff in each Health Region, each hospital's admitting physicians, acute care nurses and respiratory therapists will be invited to participate in the interactive educational program carried out by one of the Croup Clinical Practice Guideline Committee members. A "local champion" will also be identified. They will conduct educational outreach visits to physicians, nurses, and respiratory therapists who did not attend the interactive educational program.

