##### High intensity intervention

The high intensity, intervention utilizes a multi-faceted approach described by Lomas.[3] This approach uses a variety of techniques, including interactive educational meetings, educational outreach visits, reminders, identification of local opinion leaders and establishment of a local consensus process. The physician-focused multi-faceted dissemination strategy will involve identification of physician "opinion leaders" at each hospital randomized to this arm. All physicians with admitting privileges to a hospital will be asked to complete a validated questionnaire for the purpose of identifying the "local opinion leader".[4] All "opinion leaders" will be invited to participate in a workshop on the evidence for the practice guideline's recommendations and on basic principles of behaviour change.

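### The list of costed implementation time does not name the clinicians who are taught, which understates the cost of the two intensive strategies against mailing

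*Protocol article*

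**What the plan says.** The Economic analysis section of the Methods sets the scope: "An economic analysis will be carried out from a societal perspective with costs classified as either payer" or non-payer, and "The analysis will include all health care costs, costs borne by the family, and costs stemming from the strategies for implementing guidelines". The economic objective under Aim and objectives likewise counts "costs stemming from the strategies for disseminating guidelines" in total societal cost.

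Implementation strategy costs then says how the last item will be estimated. It takes the cost of publishing and posting learning materials and questionnaires. Staff time is added, described as "the time spent in meetings, organising, travel, and preparing for presentations by the Alberta Medical Association support staff"; the list of roles goes on to name "Regional Quality Assurance staff, 'local champions', opinion leaders, and any associates". On prices: "The hourly wage will be assumed to be $100 per hour for physician time", with the mean provincial wage for other health care professionals and administrators.

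The descriptions of the arms show who else gives time. In the intermediate arm, "each hospital's admitting physicians, acute care nurses and respiratory therapists will be invited to participate in the interactive educational program", which a guideline committee member carries out. A local champion then visits those who did not attend. The high intensity arm also uses meetings, outreach visits and reminders, and adds that "All physicians with admitting privileges to a hospital will be asked to complete a validated questionnaire". The low intensity arm consists of a mailing and a website.

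**The concern.** Staff time spent being taught is a resource that the strategy uses up, so a societal analysis should count it. The protocol accepts this for families: Costs to the family values missed wages, house work and travel time. The clinicians who are taught get no matching entry.

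The gap is one-sided. Session attendance, outreach visits and questionnaire completion arise only in the two intensive arms, so omitting them lowers those arms' costs and leaves mailing unchanged. Two parts of the plan depend on that contrast. One is the economic alternative hypothesis, part of which is that the intermediate strategy uses fewer resources than the low one. The other is the rule in Overview of costing methods that judges an experimental strategy cost-effective when outcomes are similar or better at lower or equal cost. An undercount on one side can move a result across that line.

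**Working it through.** The protocol states no implementation cost total, attendance, session length or cost per hospital day, so there is no figure to reproduce. The check has two parts.

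**1. People who give time, set against the costed list**

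| Who gives time | Where described | In the costed list? |
|---|---|---|
| Association support staff, regional quality staff | Intermediate intensity intervention; Implementation strategy costs | Yes |
| Local champions (outreach visits) | Intermediate intensity intervention | Yes |
| Opinion leaders (taught at a workshop) | High intensity intervention | Yes |
| Committee members who run sessions | Intermediate intensity intervention | Unclear; only if they count as associates |
| Physicians, nurses and therapists who attend or are visited | Intermediate intensity intervention; the high arm uses the same techniques | Not named |
| Physicians completing the questionnaire | High intensity intervention | Mailing is costed; answering time is not named |

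**2. Illustrative size of attendee time**

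From the document:
- Physician time is $100 an hour.
- The 30 smallest-volume Alberta hospitals diagnosed 13,750 cases, taken here to be over the six baseline years, and averaged 116 admissions per 1,000 episodes.
- Median stay is 48 hours, used here as 2 days.
- Yearly costs are divided by that year's episodes.
- Three time points are analysed: the intervention year and two follow-up years.
- Sixteen hospitals are in the intensive arms (2 × 8).

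Assumed: 15 physicians and 30 nurses or therapists per hospital, 2 hours each, $30 an hour for non-physicians, and $1,000 per hospital day.

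- Omitted cost per hospital = physicians × hours × $100 + others × hours × $30 = 15 × 2 × 100 + 30 × 2 × 30 = 3,000 + 1,800 = $4,800.
- Episodes a year in a small hospital = 13,750 / 30 / 6 = 76.4.
- Per episode in the intervention year = 4,800 / 76.4 = about $63. At half or double the attendance it is about $31 or $126.
- Averaged over three years at equal volume = 63 / 3 = about $21. At half or double the attendance it is about $10 or $42.
- At 700 episodes a year, in the intervention year = 4,800 / 700 = about $7.

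For scale, take the 25% reduction used in the power statement. The saving in hospital days in such a small hospital would be 0.116 × 2 × 0.25 = 0.058 days per episode, or about $58 per episode each year at the assumed $1,000 a day.

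Physician time alone, over a wide assumed range:

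| Attendance | Per hospital | Per episode at 100/year | Per episode at 700/year |
|---|---|---|---|
| 5 physicians × 1 h | $500 | $5 | $0.71 |
| 30 physicians × 4 h | $12,000 | $120 | $17.14 |

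Over 16 hospitals this range is $8,000 to $192,000. The per-episode columns refer to the intervention year.

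**The case against.** The wording can be read more generously. The list of people could attach only to the preparation of presentations, which would leave meeting time unrestricted, and the teaching sessions are elsewhere called meetings. A wage is set for other health care professionals, which would fit costing nurses and therapists. The article is condensed, and Overview of costing methods promises costing information in sufficient detail.

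Part of this stands. The text is not airtight, and the reference to associates may well cover the committee members who teach. But the more natural reading attaches the list to the whole series of activities. The wage is a unit price and adds nobody to the list. Associates does not naturally describe every clinician taught. The article does not defer the item to another document; it states a costing rule.

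Three stronger readings are tempting, and the document does not support them.

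- A reader might infer that only organisers' time is costed. It is not so: champions who teach and opinion leaders who are themselves taught are both listed, as are publication and mailing.
- A reader might infer that the whole economic hypothesis is favoured. Sessions and visits occur in both intensive arms, so their omission largely cancels between intermediate and high. Apart from questionnaire time, what is affected is the comparison with mailing.
- A reader might set $63 against $58 and infer that the cost ranking would reverse. That puts a one-off cost against one year's saving. It also uses the 30 smallest-volume hospitals in the province, whereas the trial hospitals were approached in rank order of episodes and hospitalization rates and six of them are large volume. Over the three analysed years, even double attendance gives about $42 against about $58 a year. The saving also leaves out family and transport costs that the plan counts.

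**Conclusion.** The point holds in this form. Followed as written, the costing rule leaves out attendee, outreach-recipient and questionnaire time, and leaves the teaching committee members' time uncertain. Under the declared societal perspective this understates the intermediate and high strategies against mailing.

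The direction follows from the text; the size does not. The illustrative figure of $4,800 per hospital rests on assumed attendance, hours and non-physician wage, and excludes questionnaire and committee-member time. Per episode it weighs most in small-volume hospitals and in the intervention year, and much less in large ones or when averaged over three years. A change in cost ranking cannot be ruled out, but nothing in the document demonstrates one. The matter concerns the economic objective and leaves the primary outcome untouched.

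**What to change.** In Implementation strategy costs, add to the costed time:

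- attendance at interactive sessions and receipt of outreach visits by physicians, nurses and respiratory therapists;
- physicians' time completing the opinion-leader questionnaire;
- preparation, travel and delivery time of the guideline committee members, either by naming them or by defining associates to include them.

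Take hours from sign-in sheets, visit logs and session lengths, and value them at the wage rules already stated. If any of this time is to be excluded on purpose, say so and justify it under the societal perspective.

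The cost is minor record keeping at sessions that will run anyway. It needs to be in place before the interventions start in August 2003, because hours are hard to recover afterwards. The downside is that the intensive strategies will look somewhat more expensive.
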